## Abstract

**Background:**

Progressive neurological diseases (PNDs) such as Parkinson disease and multiple sclerosis cause profound motor and nonmotor symptom burdens that significantly impair health-related quality of life. Beyond physical challenges, patients face profound psychospiritual distress driven by prognostic uncertainty, loss of autonomy, and existential concerns. While palliative care can address these multidimensional needs, it remains underused in neurological populations, where conventional care predominantly focuses on motor symptom management.

**Objective:**

This study aims to evaluate the effects and acceptability of a nurse-led, acceptance and commitment–based palliative program on psychological distress, psychospiritual well-being, and related health outcomes among individuals living with PNDs.

**Methods:**

This is a 2-arm, parallel-group randomized controlled trial using an explanatory sequential mixed methods design. A total of 138 participants with PNDs will be recruited and randomized 1:1 to either the intervention group (n=69) or a befriending control group (n=69). The intervention consists of five 60- to 90-minute individual sessions delivered over 3 months by trained nurses integrating acceptance and commitment therapy–based strategies (eg, mindfulness, cognitive defusion, and value-guided action) with supportive-expressive approaches. The control group receives five 30- to 60-minute active befriending sessions. The primary outcome is psychological distress, assessed via the Hospital Anxiety and Depression Scale. Secondary outcomes include spiritual well-being, meaning in life, psychological flexibility, illness perception, palliative care needs, health-related quality of life, and death anxiety. Assessments will be conducted at baseline (T0), 1 week after the intervention (T1), and 3 months after the intervention (T2). Quantitative data will be analyzed using linear mixed-effects models under the intention-to-treat principle. Following the intervention, a purposive subsample will undergo semistructured qualitative interviews to explore intervention acceptability and participant experiences.

**Results:**

This trial obtained ethics approval from the Institutional Review Board of the University of Hong Kong and was funded by the Nethersole Institute of Continuing Holistic Health Education research grant 2022-2023 and the Health and Medical Research Fund (2022), Health Bureau. Recruitment commenced in September 2023. As of manuscript submission, 132 participants have been enrolled. Data analysis has not yet commenced. The results are expected to be published in late 2026.

**Conclusions:**

This study will provide empirical evidence regarding the effectiveness and acceptability of a nurse-led, acceptance and commitment–based palliative program tailored to the complex psychospiritual trajectories of patients with PNDs. If effective, this trial will offer a scalable model for integrating structured psychotherapeutic interventions within neurology, palliative care, and community nursing practices.

## Introduction

### Background

Progressive neurological diseases (PNDs), including Parkinson disease (PD) and multiple sclerosis (MS), affect more than 8 million people worldwide [1]. These conditions are characterized by mobility dysfunctions (eg, focal weakness, rigidity, spasticity, tremors, and coordination difficulties) and nonmotor symptoms (eg, pain, fatigue, urinary dysfunction, and cognitive impairment) [2,3]. The unpredictable disease trajectory, progressive functional loss, and shifting life roles contribute to substantial psychological and spiritual distress among individuals with PNDs [3,4]. Approximately 35% to 50% of individuals with PNDs experience anxiety and depression, which are associated with impaired quality of life (QoL), accelerated disease progression, frequent relapses, and increased care dependency [4]. Furthermore, spiritual distress is highly prevalent, arising from difficulties in sustaining a sense of meaning and purpose in life while confronting existential uncertainty, functional decline, and mortality [5,6].

Despite the multifaceted nature of PNDs, conventional clinical care focuses primarily on motor symptom management within a biomedical-oriented framework, overlooking nonmotor symptoms and psychospiritual needs [2,7]. Palliative care is a specialized form of care aimed at improving QoL for patients with life-limiting illness and their families through comprehensive assessments and management of physical, psychological, social, and spiritual needs, as well as care coordination and caregiver support [8]. While international guidelines advocate for early, person-centered palliative care integration within neurology, these services remain severely underused and are frequently restricted to end-of-life care stages [7,9].

A recent systematic review and meta-analysis of 15 trials (n=3431) demonstrated that palliative care interventions significantly improved symptom burden and satisfaction with care among individuals with PNDs [10]. However, their effects on QoL remain inconclusive, and most studies have focused on advanced disease stages. Existing trials often insufficiently address psychospiritual components despite their critical role in enhancing QoL. PNDs such as MS and PD are marked by fluctuating and unpredictable trajectories characterized by sporadic exacerbations, periods of recovery, and gradual decline [11]. These complexities make conventional prognosis-based palliative care models less suitable [12] and underscore the need for early, tailored, and integrated palliative approaches that address psychospiritual distress alongside physical symptoms [13].

Chronic illnesses such as PNDs can be conceptualized as a series of disruptive events—diagnosis, symptom progression, relapses, and end-of-life transitions—that challenge individuals’ values, identity, and coping capacity [14]. Prolonged disruption may hinder psychological adjustment, underscoring the need for palliative interventions that address psychospiritual distress alongside physical symptoms [6]. The Common-Sense Model of Self-Regulation (CSM) by Leventhal et al [15] explains how individuals form illness perceptions—such as beliefs about identity (disease label and symptoms), timeline (perceived duration), causes (underlying factors), consequences (perceived impacts of disease on everyday life), and control (the sense of agency in managing the disease)—that shape coping and outcomes. Additional dimensions include coherence (understanding of the illness) and emotional representations (emotional impact). Individuals with PNDs often perceive their condition as chronic, unpredictable, and uncontrollable, which can intensify helplessness and distress [16,17]. The prolonged disease duration, unpredictability of disease progression, and lack of definitive causes or cures further diminish one’s sense of control. Negative illness perceptions are associated with psychological distress, maladaptive coping, and poor treatment adherence [18,19], although coping strategies and social support may moderate these effects. Interventions that promote more adaptive illness representations and a greater sense of agency may therefore enhance coping and improve health outcomes [19,20].

Managing Cancer and Living Meaningfully (CALM) therapy is a brief, semistructured, and individualized psychotherapeutic intervention designed to alleviate distress and enhance psychological growth in patients with advanced cancer [21]. It focuses on four broad, interrelated domains in the context of living meaningfully with a life-threatening illness: (1) symptom management and communication with health care providers; (2) changes in the self and relations with close others; (3) spiritual well-being and sense of meaning and purpose; and (4) preparing for the future, sustaining hope, and facing mortality. Delivered over 3 to 6 therapist-led sessions, CALM uses a supportive-expressive approach to foster reflection, cognitive reframing, and meaning finding, facilitating mentalization—an ability to reflect on feeling states, differentiate from literal facts, and accept the possibility of multiple perspectives—which is crucial for patients to sustain hope and engage in disease planning and a meaningful life despite their illness. Empirical evidence demonstrates CALM’s effectiveness in reducing depressive symptoms, enhancing end-of-life preparedness, and improving overall QoL in patients with cancer [21]. Participants described CALM as a “safe place” for them to be “seen as a whole person” and that supports them to live meaningfully and “handle death issues in a peaceful way.” However, adaptation is required for individuals with PNDs, whose illness trajectories are prolonged, fluctuating, and marked by recurring losses. While CALM addresses existential concerns, many aspects of PNDs remain uncontrollable, and persistent uncertainty may intensify helplessness. Attempts to suppress distressing thoughts may paradoxically intensify psychological distress [22]. Thus, coping in PNDs requires not only meaning-centered exploration but also acceptance of ongoing uncertainty and decline.

Acceptance and commitment therapy (ACT), a third-wave cognitive behavioral therapy, conceptualizes psychological distress as arising from attempts to avoid or control unwanted internal experiences, which in turn restricts engagement in meaningful activities [22]. ACT aims to enhance psychological flexibility—the ability to accept internal experiences while pursuing value-based action—through 6 psychological processes: defusion, acceptance, contact with the present moment, the self as context, values, and committed actions [22]. Using experiential exercises, mindfulness, and metaphors, ACT helps individuals relate differently to distressing thoughts and emotions [22]. Acceptance- and mindfulness-based interventions have shown promise in promoting emotional balance and mental clarity through the cultivation of nonjudgmental awareness [23]. ACT has demonstrated effectiveness across chronic conditions, including chronic pain and diabetes, as well as common mental disorders [24]. Emerging evidence in palliative populations is also encouraging: a systematic review of 6 studies involving 261 patients with advanced cancer reported improvements in symptoms, psychological distress, and QoL [24]. Higher levels of acceptance are associated with more adaptive coping and fewer psychological morbidities and avoidance behaviors, supporting psychological flexibility as a protective factor in the face of serious illness [25].

Building on the empirical support for CALM therapy and ACT, we propose integrating these approaches to address the psychospiritual needs of individuals with PNDs. CALM therapy provides a structured framework to explore practical and existential concerns—such as symptom management, communication, and prognostic uncertainty—while fostering meaning and hope in the context of serious illness. However, many aspects of PNDs, including progressive decline and mortality, remain beyond personal control, and patients may become entangled in distressing thoughts and emotions that restrict engagement in meaningful activities. ACT complements this framework by cultivating acceptance and psychological flexibility, enabling patients to relate differently to difficult internal experiences and continue pursuing value-based living despite uncertainty and loss. Integrating these approaches may therefore help individuals with PNDs navigate distress, sustain meaning, and adapt more flexibly to disease progression.

Accordingly, this study aims to develop and evaluate a novel, nurse-led palliative intervention that integrates acceptance and commitment–based strategies within a supportive-expressive framework. The primary objective is to alleviate psychological distress; cultivate psychological flexibility; and optimize the multidimensional, psychospiritual well-being of individuals living with PNDs.

### Aims and Hypotheses

This study aims to (1) examine the effects of a nurse-led, acceptance and commitment–based, supportive-expressive palliative care program on anxiety and depressive symptoms (primary outcomes) and spiritual well-being, meaning in life, palliative care needs, psychological flexibility, illness perception, health-related QoL, and death anxiety (secondary outcomes) among individuals with PNDs compared to a befriending control group; and (2) explore participants’ perceptions and experience of the palliative program, specifically identifying its perceived utility, mechanisms of change (how and why it works or fails to work), and contextual factors influencing intervention acceptability, motivation, and real-life practice.

It is hypothesized that individuals with PNDs who receive the palliative program will demonstrate significantly greater improvement in psychological distress at the postintervention follow-up (T1) and 3 months after the intervention (T2) compared with those receiving the befriending control. In addition, it is hypothesized that participants in the palliative program will show greater positive changes in secondary psychological, spiritual, and palliative outcomes relative to the control across the same time points.

## Methods

### Study Design, Setting, and Sampling

This sequential mixed methods study comprises a 2-arm randomized controlled trial followed by a qualitative study. This protocol adheres to the SPIRIT (Standard Protocol Items: Recommendations for Interventional Trials) checklist [26]. Adults with PNDs will be recruited from outpatient neurology clinics (Queen Mary Hospital and Tung Wah Hospital) and patient support groups (Hong Kong Parkinson’s Disease Foundation and Hong Kong Neuro-Muscular Disease Association) in Hong Kong.

Eligible participants are adults (≥18 years) diagnosed with PNDs (eg, PD, MS, motor neuron disease, multiple system atrophy, progressive supranuclear palsy, muscular dystrophy, spinocerebellar ataxia, or spinal muscular atrophy) with psychological distress indicated by a Hospital Anxiety and Depression Scale score of 8 or higher on either the depression or anxiety subscale (sensitivity and specificity of 0.75‐0.89) [27] and able to communicate in Cantonese.

Exclusion criteria are severe cognitive impairment (Abbreviated Mental Test <6) [28], recent psychotherapy (within 6 months), or severe psychiatric or medical comorbidities limiting participation.

Power analysis using G*Power was performed to estimate the required sample size. Previous studies of mindfulness- and acceptance-based interventions have reported large effect sizes (0.96‐1.14) in people with MS [29] and moderate to large effects for anxiety (*d*=0.58) and depression (*d*=0.74) in PD [30]. Given the use of an active control (befriending), a conservative moderate effect size of 0.58 was assumed for the primary outcome (anxiety and depressive symptoms). Using a Bonferroni-adjusted significance level of 2.5% and 80% power, 118 participants (59 per arm) are required. Allowing for 15% attrition, the final target sample size is 138 participants (69 per arm).

For the subsequent qualitative phase, approximately 30 participants from the intervention group will be invited for postprogram semistructured interviews, with the final sample size guided by data saturation. Purposive maximum variation sampling (eg, gender, age, and educational level) will be used to capture diverse experiences. Additional participants will be recruited until no new themes emerge.

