### Data Collection Procedure

Potential participants will be provided with a general overview of the study. A research assistant will set an appointment with those patients who meet the inclusion criteria and agree to participate in the study. In the face-to-face interview, a research nurse will check the eligibility criteria and perform the baseline evaluation (T0). Information on all screened patients and reasons for exclusion will be recorded. Participants will receive a cash reward of HKD 100 (approximately US $13) per each assessment (T0, T1, and T2). To control for participant expectancy, both groups will be introduced with identical positive phrasing regarding the potential benefits of the interventions. After baseline assessment, participants will be randomly assigned to the 2 groups on a 1:1 basis using the method of permuted block with random block sizes of 4, 6, and 8 by an independent researcher not involved in the assessments. The allocation list will be computer generated by an independent researcher and concealed from other researchers and participants until the time of assignment. An independent research assistant blinded to the group allocation will collect the postintervention questionnaires. Figure 1 shows the flowchart of the study implementation plan.

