### Data Analysis

Quantitative data will be analyzed using SPSS (version 28.0.1; IBM Corp) following the intention-to-treat principle. Descriptive statistics will summarize baseline characteristics, and group comparability will be examined using chi-square or Fisher exact tests. Linear mixed-effects models will assess intervention effects on primary and secondary outcomes, with time, group, and group-by-time interaction included as fixed effects. Between-group differences will be estimated using linear contrasts. Model assumptions will be checked using normal probability plots. Missing data will not be imputed as mixed-effects models accommodate incomplete observations [48]. A 2-sided significance level of 5% will be adopted. To account for the variations in therapist contact and attention, we will log the exact duration (in minutes) of each session for every participant. In sensitivity analysis, total contact time will be included as a covariate in the linear mixed-effects models to statistically control for the potential confounding effect of extra nurse contact.

Qualitative interviews will be transcribed verbatim and managed using NVivo (version 12; Lumivero). Two researchers will independently conduct inductive thematic analysis following a 5-step approach [49]. Codes will be organized into categories and themes to identify recurring patterns. An audit trail will enhance rigor, and discrepancies will be resolved through discussion. Qualitative findings will complement and enrich interpretation of the quantitative results.

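### The sample size rests on a single-step Bonferroni level of 2.5%; testing the two primary outcomes by Holm would add about 4 to 5 points of power for anxiety on the planned effects, and would reconcile that level with the 5% stated for analysis

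*Protocol article*

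**What the plan says.** Study Design, Setting, and Sampling gives the sizing: "Using a Bonferroni-adjusted significance level of 2.5% and 80% power, 118 participants (59 per arm) are required". Bonferroni is the only multiplicity method the article names, and it appears only there. What the 5% is divided over is not spelled out. Aims and Hypotheses lists "anxiety and depressive symptoms (primary outcomes" in the plural, which makes a split over two outcomes the natural reading. The abstract instead has a single outcome: "The primary outcome is psychological distress, assessed via the Hospital Anxiety and Depression Scale". The hypothesis also covers two time points: "significantly greater improvement in psychological distress at the postintervention follow-up (T1) and 3 months after the intervention (T2".

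On effect sizes, the sizing paragraph cites "moderate to large effects for anxiety (*d*=0.58) and depression (*d*=0.74) in PD [30" from an earlier study, but plans on one value for both components: "a conservative moderate effect size of 0.58 was assumed for the primary outcome (anxiety and depressive symptoms".

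Data Analysis states "A 2-sided significance level of 5% will be adopted" and attaches no multiplicity rule to it.

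**The concern.** Single-step Bonferroni holds the second outcome to 2.5% even after the first has been rejected. Holm tests the smaller p-value at 2.5% and, once that is rejected, the larger at 5%. It rejects everything Bonferroni rejects and sometimes more. It controls familywise error at the same 5% and needs no assumption about the correlation between the two subscales of the Hospital Anxiety and Depression Scale.

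If the sizing level becomes the testing rule, an anxiety result with p between 0.025 and 0.05 beside a clearly positive depression result would be declared non-significant, although error control does not require it. If the 5% in Data Analysis is applied to each outcome, the protection that the sizing paid for is lost. Recruitment is nearly complete (132 enrolled as of January 2026, according to Results), so the choice of test is one of the few remaining ways to gain power.

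**Working it through.** **Inputs.** From the article: standardised effect 0.58 for both components, two-sided 2.5%, 80% power, 1:1 allocation, 59 per arm; cited but not planned on, 0.74 for depression. Assumed: a correlation between the two subscales of 0.3 to 0.7, because the article gives none. The model is a two-sample t-test at one time point, which matches the sizing and is not the planned mixed model.

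**1. The plan's own figure.** The normal approximation is n per arm = 2(z₀.₉₈₇₅ + z₀.₈₀)²/d² = 2(2.241 + 0.842)²/0.58² = 56.5, so 57. The noncentral t gives 58, against 59 stated, so the figure reproduces. Two-sided 5% would need only 48, so the 2.5% level did set the sample size. For attrition, 118/0.85 = 138.8, against 138 stated.

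**2. Power for anxiety at 59 per arm.** It is 80.9% at 2.5% and 87.8% at 5%. The most any step-down rule could recover is therefore 87.8 − 80.9 = 6.9 points.

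**3. What Holm adds.** Power for anxiety under Holm = P(p_anx < 0.025) + P(0.025 ≤ p_anx < 0.05 and p_dep < 0.025). The second term is the gain. If the outcomes were independent, it would be 6.9 points times the power for depression at 2.5%:
- depression 0.58: 0.069 × 0.809 = 5.6 points
- depression 0.74: 0.069 × 0.959 = 6.6 points
- depression 0.30: 0.069 × 0.265 = 1.8 points

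**4. With correlation.** Simulation of the two correlated t statistics, 1,000,000 draws per setting, correlation 0.3 to 0.7:

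| True effects (anxiety / depression) | Anxiety, Bonferroni | Anxiety, Holm | Both, Bonferroni | Both, Holm |
|---|---|---|---|---|
| 0.58 / 0.58 | 81% | 85-86% | 68-72% | 78-81% |
| 0.58 / 0.74 | 81% | 87% | 78-80% | 86-87% |
| 0.58 / 0.30 | 81% | 81-82% | 24-26% | 34-36% |

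The anxiety gain is 4.1 to 5.0 points on the first row and about 6.5 on the second (6.3 to 6.6 over correlations of 0 to 0.8). On the third row it is about 1 point or less. If depression has no effect, it is 0.1 to 0.2 points. The chance of showing at least one outcome is identical under the two methods in every row, because both start with the smaller p-value at 2.5%.

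**5. Error under the global null.** Familywise error is 4.3% to 4.8% and identical for Bonferroni and Holm. With 5% applied to each outcome, it is 8.4% at correlation 0.7, 9.1% at 0.5 and 9.5% at 0.3. The independent case is 1 − 0.95² = 9.75%.

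**The case against.** The best defence is that nothing in the sizing sentence is wrong. Its number reproduces, and sizing at half of alpha is a sound conservative choice even when a step-down test is planned. The article does not say that Bonferroni will be the analysis rule, and a fuller protocol or analysis plan may specify another. This stands. A reader might infer that the trial will reject anxiety results between 0.025 and 0.05, but Data Analysis, taken literally, would call such a result significant. The loss of power is therefore conditional on the 2.5% being carried through.

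A reader might also put the loss at 6 to 7 points. That needs depression at 0.74, a value the article cites and then sets aside for 0.58 because the control is active. The upper end, 6.9, is a ceiling that Holm does not reach.

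The two-outcome family is itself inferred. The 2.5% could have been meant for T1 and T2, in which case the anxiety and depression figures do not describe the split.

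The defence does not remove the point. The two levels in the article lead to different verdicts on the same data, and Holm improves on either one: it adds power if 2.5% is used throughout, and it restores familywise control if 5% is used for each outcome.

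**Conclusion.** The point holds as a low-cost improvement; it does not show that the trial is undersized or the sizing invalid. If the 2.5% split is used for testing, Holm raises power for anxiety by about 4 to 5 points on the planned effect of 0.58 for both outcomes, and power for both outcomes by about 8 to 10 points. At the cited 0.74 for depression, the anxiety gain is about 6.5 points. It nearly vanishes if depression responds little. If 5% per outcome is used instead, familywise error is about 8-9%, and Holm holds it to at most 5%.

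These sizes rest on a two-outcome family, an assumed correlation of 0.3 to 0.7, 59 evaluable per arm and a t-test at one time point. That Holm rejects at least as much as Bonferroni at the same familywise error depends on none of these.

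**What to change.** In Data Analysis, before outcome data are analysed (Results reports that none have been), state that the two primary p-values, for anxiety and for depressive symptoms, are tested by Holm at a familywise two-sided 5%: the smaller at 2.5% and, if it is significant, the larger at 5%. Say which contrast supplies each p-value. If the primary family is defined with more tests, for example both outcomes at both time points, apply Holm to the whole family.

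Keep the 2.5% sizing and the target of 138. For two tests, 2.5% is Holm's strictest step, so the stated power is a lower bound. With four tests the first step would be 5%/4 = 1.25%, and the sizing would no longer cover that worst case.

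The cost is one sentence, with no extra patients or data. The drawback is that simultaneous confidence intervals matching Holm are less simple than Bonferroni intervals. Ordinary 95% intervals reported beside Holm-adjusted p-values would do, with a note that the intervals are not adjusted for multiplicity.
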